#### Vitamin D axis function

We will evaluate vitamin D axis function through changes in 1,25(OH)_2_D [22] levels from blood collected at specified times following surgery. Based on our previous work, we anticipate a 40 % intra-operative decline in 1,25(OH)_2_D levels [8] and some children will experience a transient decline in 1,25(OH)_2_D levels into the deficient range (<50 pmol/L). Given adequate 25OHD levels and an otherwise properly functioning vitamin D axis, we anticipate restoration (or maintenance) of active hormone levels into the normal range within 12 hours of surgery. Impaired vitamin D axis function will be defined as an inability to maintain active hormone levels in the normal range at any point from blood work collected after the first postoperative day.

#### Organ function and ICU outcome measures

Postoperative cardiovascular and immune function will be measured and compared between the two groups. Cathelicidin levels, an endogenous antimicrobial peptide, will be used as a surrogate measure of innate immune function [40, 41, 67]. Clinically relevant measures of cardiac organ function including echocardiograms (for example, ejection fraction), inotrope requirements (for example, vasopressor need or maximum inotrope score) and fluid resuscitation (positive fluid balance in first 48 hours). Further, we will also evaluate standard PICU clinical outcome measures including time to extubation and PICU and hospital lengths of stay.

#### Phase III study feasibility

We will determine the feasibility of a subsequent multicenter large interventional study through an evaluation of study recruitment rate, proportion of protocol violations, proportion of adequate allocation concealment and blinding, proportion of study drug compliance, and proportion of study drop out.

### Study procedures

A summary of study procedures, biological sample collection and metabolite measurements has been provided as a flow diagram (Fig. 1) and the biochemical measurements on research specimens are summarized in Table 4.

**Fig. 1 Fig1:**
[figure not shown]
Flow chart of study-related procedures and measurements. Patients and/or caregiver may decline initiation blood work and urine samples and still participate. Postoperatively, urine will only be collected at PICU admission if it was not collected in the operating room. Participants with isolated postoperative hypercalciuria will only have renal ultrasound at the request of nephrology. CHD, congenital heart disease; PICU, Pediatric Intensive Care Unit; POD, postoperative day

**Table 4 Tab4:** Biochemical measurements on research specimens

Sample	Timepoint				
	Pre-treatment^a^	During study drug administration^b^	Preoperative^c^	Operating room prior to surgery	Postoperative
Blood	Vitamin D^d^	Vitamin D^d^	Vitamin D^d^	Vitamin D^d^	Vitamin D^d^
		Ionized calcium	Ionized calcium	Ionized calcium	Ionized calcium
				VDBP	VDBP
				PTH	PTH
				Immune function	Immune function
				(for example, cathelicidin)	(for example, cathelicidin)
				Immune activity	Immune activity
				(for example, cytokines)	(for example, cytokines)
Urine	Calcium to	-	-	Calcium to	Calcium to
	Creatinine ratio			Creatinine ratio	Creatinine ratio

^a^neonates, or < 2 months of supplement anticipated

^b^any patient who receives > 6 months of supplement

^c^all outpatients who receive > 2 months of supplement

^d^25OHD will be measured to indicate vitamin D status. The 25OHD level determined at the time of standard preoperative blood work, for safety purposes, will be ordered through the laboratory. The intraoperative and postoperative 25OHD measurements will be determined, using LC-MS/MS technology that adheres to and meets the standards of the Vitamin D External Quality Assessment Scheme

#### Prior to initiation of study drug

**Urine** - After consent is obtained and the study participant is waiting for the pharmacy to prepare the study drug, we will gather a urine sample for determination of calcium:creatinine ratios. Where developmentally appropriate, the participants will be asked to provide urine into a container. Urine bags will be placed on younger children. If the child is unable to provide a urine sample during the time it takes to fill the study drug prescription, the participant will be provided with a container or urine bag and asked to provide an outpatient urine sample.

**Blood** - Neonates and other study participants requiring surgery within 2 months of diagnosis and enrollment will have 0.5 to 1 mL of blood collected prior to (or within 2 days) of starting the study supplement for determination of 25OHD. Where possible, unused or discarded blood will be obtained from the laboratory [68]. If unused blood is not available, research blood will be collected at the time of clinically indicated blood work, or not at all. These patients will not have blood collected for research purposes again until they are taken to the operating room.

* Note - We will request initiation samples but children will still be enrolled if these samples cannot be collected or the families do not want these procedures.

#### During period of study drug administration

All outpatient participants will have blood collected at the time of standard presurgical blood work (2 to 3 weeks prior to surgery) for both 25OHD and ionized calcium. These samples are collected to ensure that patients do not go for surgery with potentially toxic levels of vitamin D. The safety officer will review the ionized calcium level on the patients chart, and follow up if required, as per the safety measures outlined in the sections below. For those participants who will receive the study drug for more than 6 months, we will measure 25OHD and calcium, and they will also have additional blood work to ensure that potentially toxic levels are not maintained for long periods prior to surgery. The timing of this blood work will not be specified and will occur as part of clinically indicated blood work during regularly scheduled clinic appointments

#### Intraoperative biological samples and measurements

**Blood** - All study participants will have 2 mL of blood collected in the operating room following anesthesia and intubation, but prior to skin incision and initiation of cardiopulmonary bypass. Preoperative ionized calcium will be determined. Remaining sample will be aliquoted and stored at -80 °C for determination of 25OHD at the end of the study.

**Urine** - All study participants will have urine collected after insertion of the urinary catheter and the calcium:creatinine ratio will be determined. Study results will not appear on the patient hospital chart, but will be labeled with the study ID number and forwarded to the study investigator and safety officer for review.

#### Postoperative biological samples and other study measurements

**Blood** - All study participants will have 2 mL of blood collected following separation from cardiopulmonary bypass (at admission to PICU). Table 4 shows the biomarkers to be measured. Further, study participants will have 2 mL of blood collected on postoperative days 1, 3, 5 and 10 in the PICU. Samples will be collected from arterial or central venous catheters at the time of clinically indicated blood work. If these catheters have been removed, blood will be collected at the time of clinically indicated venipuncture. If patients are discharged to the ward before the day 10 research sample is collected, a discharge sample will be collected at the time of discharge and no further research blood will be gathered. To limit the volume of research blood collected, neonates will only have 1 mL of blood collected postoperatively on days 3, 5, and 10.

**Urine** - All study participants will have urine collected from the urinary catheter on the first postoperative day. Calcium and creatinine concentrations will be determined.

**Echocardiography** - A comprehensive exam will be performed immediately postoperatively (standard of care) and on the first postoperative day by a trained technician or pediatric cardiologist. Between-group comparisons will evaluate for differences in left-ventricular in (LV) end-diastolic diameter, LV end-systolic diameter, and LV ejection fraction [34].

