#### Study objectives

The primary and secondary objectives are as follows:The primary objective is to perform a double-blind RCT to determine whether the preoperative administration of a daily high dose of vitamin D, based on the UL from IOM [46], compared with usual care, results in a significant reduction in postoperative vitamin D deficiency in a pediatric population with CHD.Secondary objectivesDetermine whether the preoperative regimen of daily high dose vitamin D, compared with usual care, results in a greater number of vitamin D related adverse events (hypercalcemia, hypercalciuria).Determine whether the preoperative regimen of daily high dose vitamin D, compared with usual care, improves established markers of vitamin D axis functioning (active hormone levels, cardiac function).Determine the barriers and feasibility of conducting a larger phase III RCT evaluating whether vitamin D supplementation improves clinical outcomes in children who require CHD surgery (blinding, recruitment, and compliance).

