### Anticipated duration of study drug and perioperative 25OHD levels

#### Duration of study drug

Vitamin D supplementation is generally initiated within a week of birth, so the duration of preoperative therapy would be from birth (or diagnosis of CHD) to the time of surgery. Timing of surgery is very dependent on the type of CHD lesion. Consistent with the literature, our recent observational study of perioperative vitamin D status demonstrated 8 months as the median age at surgery, with 2.4 months being the 25th percentile. Based on these findings, we anticipate that it should be possible for 75 to 80 % of patients to receive study drug for more than 2 months (the time required to achieve a new 25OHD steady state with high dose daily supplementation). Whether this duration of study drug can actually be achieved preoperatively and the 25OHD levels achieved will be reported as part of the pilot study.

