### Randomization, blinding and stratification procedures

We will use a computer-generated randomization sequence. Only the CHEO pharmacy will have access to the randomization sequence and will be responsible for participant randomization and allocation. Only the pharmacist will know the identity of the study drug administered to specific patients. Given the expected recruitment (two to three per month) and potential impact of season on 25OHD, randomization will be performed in permuted blocks (four within each stratum). We will blind patients, families, investigators, hospital staff, and research personnel to treatment arm. Blinding was considered necessary to avoid (i) families altering the outpatient dose and (ii) a number of secondary outcome measures are that are potentially subjective (echocardiography, timing of extubation, need for fluids or catecholamine infusion). Within each age group, the two interventions will be indistinguishable (vial, volume, color, taste, consistency and smell).

Participants will be stratified into whether or not they are expected to receive at least 8 weeks of study drug prior to surgery. This stratification should guarantee that an equal number of CHD patients who will not receive 8 weeks of oral dosing end up in both the high and low dose arms. We will further stratify by age (under or over 1 year of age).

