### Statistical analysis

#### Sample size justification

Based on our observational studies and findings from recent dose evaluation studies on healthy children, we estimate that no more than 40 % of the usual care arm will have postoperative 25OHD levels above 50 nmol/L. Based on the 25OHD levels achieved with 1600 IU/day in recent studies on approximate IOM high dose in healthy children, we anticipate that 80 % of the high dose arm will have postoperative levels above 50 nmol/L. Therefore group sample sizes of 28 in both treatment arms will be required to achieve 80 % power to detect an absolute difference between the group proportions of 0.40. The test statistic used is the two-sided Fisher’s exact test and the significance level of the test was targeted at 0.05. Assuming a 10 % drop-out rate, approximately 62 patients (total) will need to be recruited.

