#### Secondary outcomes

Secondary analyses will be evaluated between groups based on data type. Outcome measures that are continuous will be evaluated using the *t*-test, Wilcoxon sign rank test (where appropriate) or through linear regression analysis if important variables are not evenly distributed between groups. Binary secondary outcome measures (for example, hypercalcemia, hypercalciuria) will be compared between the two treatment groups using Fisher’s exact or Chi-square. For the analysis of outcomes measures that represent time to event (for example, restoration of 1,25OH_2_D levels to normal range, time to extubation, and PICU length of stay/discharge), we will apply the log rank test. If randomization does not lead to equal distribution of important variables (for example, weight) the analysis will be expanded to multiple regression modeling (for example, logistic, linear, Cox proportional hazard).

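### Two of the three echocardiographic comparisons scale with body size, and the stated weight adjustment applies only when the arms are imbalanced, so both lose precision

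*Protocol article*

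**What the plan says.** The Study objectives section makes it a secondary aim to see whether the high dose "improves established markers of vitamin D axis functioning (active hormone levels, cardiac function"). The Echocardiography paragraph (Postoperative biological samples and other study measurements) names the variables: "Between-group comparisons will evaluate for differences in left-ventricular in (LV) end-diastolic diameter, LV end-systolic diameter, and LV ejection fraction". Organ function and ICU outcome measures describes a broader set: "Clinically relevant measures of cardiac organ function including echocardiograms (for example, ejection fraction), inotrope requirements (for example, vasopressor need or maximum inotrope score"), together with fluid balance over the first 48 hours.

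Eligibility runs from 36 weeks gestational age to 18 years (Study population, Inclusion). The authors' earlier cohort had "8 months as the median age at surgery, with 2.4 months being the 25th percentile" (Duration of study drug). Allocation uses one age cut: "We will further stratify by age (under or over 1 year of age").

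The Secondary outcomes analysis section gives continuous measures a t-test or a Wilcoxon test, "or through linear regression analysis if important variables are not evenly distributed between groups". It then repeats the condition with weight as its example: "If randomization does not lead to equal distribution of important variables (for example, weight) the analysis will be expanded to multiple regression modeling". The article does not mention z-scores, body surface area or any other size indexing.

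**The concern.** LV end-diastolic and end-systolic diameters are lengths. In a sample that mixes young infants with school-age children and adolescents, much of the spread in these lengths reflects how big the child is. An unadjusted two-sample test puts that spread in its standard error.

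The conditional rule does not help, because it responds to a different problem. Imbalance between arms moves the estimate. Size variance within arms widens the interval, and it does so even when mean weight is identical in the two arms. Stratifying at 1 year makes imbalance in size less likely, so the regression becomes less likely to be triggered, while the within-arm spread remains. The analysis section does not carry the age stratum into the test either.

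What is at stake is precision for two secondary measures in a pilot that is meant to inform a larger trial. A null result for the diameters would be uninformative, with a wide interval.

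**Working it through.** **The plan's own figure.** No sample size is given for the echocardiographic measures; 28 per arm comes from the primary outcome. The usual-care input there is "no more than 40 % of the usual care arm will have postoperative 25OHD levels above 50 nmol/L", against 80% in the high-dose arm. Exact two-sided Fisher power for 0.40 versus 0.80 is 0.799 with 26 per arm, 0.802 with 27 and 0.823 with 28. The continuity-corrected formula also gives 28. For the total, 56 × 1.1 = 61.6, so 62, and 56/0.9 = 62.2, so 63. The stated 62 is reproduced within tolerance, and 28 per arm is used below.

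**Inputs from the article.** Median age at surgery 8 months, 25th percentile 2.4 months, upper age limit 18 years, 28 per arm. The two-sided 5% level and 80% power are those of the primary calculation.

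**Assumptions, not in the article.**
- Age at surgery is lognormal, cut at 18 years. Log SD = ln(8/2.4)/0.6745 = 1.785. After the cut, the simulated quartiles are 2.3, 7.5 and 23.3 months.
- Body weight follows a typical curve from 3.4 kg at birth through 9.7 kg at 1 year to 63 kg at 18 years.
- Diameter is proportional to weight to the power 0.25, 0.33 or 0.40.
- Residual coefficient of variation at a given size is 8-15%.

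**Size spread.** The simulated SD of log diameter due to size alone is 0.148, 0.197 and 0.236 for the three exponents.

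**Formulas.** Total SD = √(size SD² + residual²). Detectable ratio = exp[(1.960 + 0.842) × √(2/28) × SD] = exp(0.749 × SD).

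- Most favourable unindexed case: √(0.148² + 0.08²) = 0.168; exp(0.749 × 0.168) − 1 = 13.4%.
- Least favourable unindexed case: √(0.236² + 0.15²) = 0.280; exp(0.749 × 0.280) − 1 = 23.3%.
- Size-standardized: exp(0.749 × 0.08) − 1 = 6.2%, up to exp(0.749 × 0.15) − 1 = 11.9%.

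| Analysis | Detectable difference, 28 per arm | Power for a log difference of 0.10 (about 10%) |
|---|---|---|
| Unindexed | 13-23% | 0.27-0.61 |
| Age stratum only in the model | 9-17% | 0.44-0.87 |
| Size-standardized | 6-12% | 0.70 to above 0.99 |

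Body size accounts for 49-90% of the variance in log diameter over these settings. The number per arm needed for 80% power at a log difference of 0.10 is 45-124 unindexed and 11-36 size-standardized. The size-standardized figures are a best case, because they assume that standardization removes all of the size variance.

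**Sensitivity to a larger residual.** Take the middle exponent and an assumed residual of 30%. Total SD = √(0.197² + 0.30²) = 0.359. Detectable difference = exp(0.749 × 0.359) − 1 = 31% unindexed, against exp(0.749 × 0.30) − 1 = 25% standardized. The size share falls to 0.0388/0.1288 = 30%, and the gain in effective sample size is 0.1288/0.09 = 1.4-fold.

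**Ejection fraction.** This is a ratio and does not scale with size. Its detectable difference is 0.75 SD with 28 per arm under either analysis.

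**The case against.** The strongest reply is that the article nowhere says the diameters are unindexed. Expressing a paediatric diameter as a z-score is a derivation detail that a condensed article may leave to the full protocol or analysis plan. That stands in part: a reader might infer that the sponsor has committed to raw millimetre values, and the text does not say so. But the article does more than stay silent. It fixes how body size enters the analysis of continuous secondary outcomes, namely only on imbalance, and that rule does not address within-arm size variance. The article also sets age-specific limits for calcium and for the calcium:creatinine ratio in Table 3, with nothing comparable for the diameters.

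A reader might also infer that body size swamps any drug effect, or that the cardiac objective cannot be answered. The documents do not support that. The same sentence lists ejection fraction, and inotrope requirement and fluid balance are assessed as well.

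Nor should one infer that a chance size difference would pass for a cardiac effect. Under randomization, size adds noise that the standard error already reflects, so type I error is not inflated. The regression on weight is foreseen for the imbalance case.

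The remaining objections also have weight. The growth and residual figures are assumed. Mixed lesions measured soon after bypass could have a larger residual spread. The trial is a pilot powered for postoperative 25OHD, so nothing here touches its primary conclusion.

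**Conclusion.** The point holds as a loss of precision in two secondary comparisons. Followed as written, a trial with balanced arms compares LV end-diastolic and end-systolic diameter with body-size variance left in the error.

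Under the stated assumptions this roughly doubles the detectable difference, from 6-12% to 13-23% of the mean diameter with 28 per arm. Putting the age stratum in the model recovers only part of the loss (9-17%). The direction needs only that the diameters grow with the child. The size depends on growth and residual-spread figures that the article does not give, and the gain narrows as residual spread rises. There is no bias, and neither the primary outcome nor the other cardiac measures are affected.

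**What to change.** State that both diameters are analysed, for every participant and regardless of balance, in one of two ways:

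- as size-standardized z-scores from one named reference, compared between arms with the age stratum in the model; or
- as log diameter in a linear model with treatment, log weight and the age stratum always included.

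Leave ejection fraction as it is.

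The cost is a sentence or two of analysis wording and no new visit, sample or scan. The z-score reference or model form must be fixed before unblinding. Body weight must be recorded close to surgery, and height too if the z-scores use body surface area. The Case report form section lists neither, and height appears nowhere in the article. For children already enrolled (62% of target at the time of writing), these values may have to come from the hospital record. The log-weight model is therefore the less demanding option. Weight at surgery is measured after randomization, so using it assumes that the supplement does not itself alter growth; that assumption should be stated.

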#### Case report form

All trial information will be stored in a secure electronic database to maintain confidentiality. Data entry methods are in place to promote data quality. In addition, protocol deviations, including discontinuation of study participation, will be recorded. The case report form will be developed using REDCap [69]. Research Electronic Data Capture is a secure web application for building and managing online surveys and databases. The following data will be entered electronically:*Questionnaire -* On the day of surgery the research coordinator will collect the participant dairies and unused study supplement. The patient diaries will contain information on which days the patient was given the study drug, why not, and whether there were difficulties. Information will also be collected on prescribed medications, nutrition, additional supplement use, and symptoms associated with vitamin D intoxication (for example, constipation or abdominal discomfort).*Operative details -* The research assistant will extract detailed operative information, including the following: cardiac lesion type, surgery performed, RACHS score [70], total fluid intake and output, blood product and fluid administration and loss, hypothermia, need for deep hypothermic circulatory arrest (duration), aortic cross clamp times, CPB circuit volumes, CPB circuit constituents, CPB time, occurrence of intraoperative hyper or hypocalcemia, administration of parenteral calcium, need for catecholamines following separation from CPB, and occurrence of intraoperative arrhythmias.*PICU course -* Clinically relevant information on clinical course and organ dysfunction will be collected, including: death, ECMO, PRISM illness severity [71], cardiovascular dysfunction (fluid bolus requirements, inotrope/catecholamine use, arrhythmia), renal dysfunction (urine output, creatinine measurements, need for dialysis), hypocalcemia and calcium administration, duration of mechanical ventilation and duration of PICU stay.

